#### 2.3.2. Spatial Characterization of Vegetation Structure (LiDAR)

LiDAR scans have been and will continue to be acquired periodically as the microforest gets established. An initial LiDAR scan was performed in August 2022 utilizing a drone (Figure 2). This was followed by a scan in January 2023, prior to construction, and another in May 2024 during construction. The last two scans utilized a backpack LiDAR device to more effectively capture vegetation density, which will also be used for future scans. The LiDAR data will allow for the structural characterization of vegetation density, canopy development, and quantification of three-dimensional vegetation before and after intervention.

### 2.4. Biological Data Collection

#### 2.4.1. Avian Surveys

To establish baseline biodiversity and enable longitudinal comparison, avian surveys were conducted prior to intervention. For comparison, data were also collected from two other Louisville green spaces: the University of Louisville Humanities Quad and Nettleroth Bird Sanctuary in Cherokee Park. From February through April 2024, each site was visited >15 times (morning and late afternoon/early evening), with 30 min observation periods per visit. Birds were identified to species visually using high-quality binoculars (Swarovski CL Companion 8 × 30, Vortex Razor UHD 10 × 42, Eagle Optics Ranger ED 10 × 42, and Nikon 10 × 42). The abundance of each species was also estimated.

#### 2.4.2. Soil Microbiome Data and Greenhouse Gas Fluxes

Soil microbial activity and gas fluxes were assessed using a Los Gatos Research Ultraportable GHG Analyzer to measure CO_2_, CH_4_, and water vapor concentrations (the latter for correction). Flux chambers (~5.7 L and ~4.6 L volumes) connected to soil collars (27 and 22 cm diameter) allowed solar penetration and captured plant–soil gas exchange. Net emissions were inferred from increasing chamber concentrations, while decreasing levels indicated uptake. To minimize disturbance, collars were set 30 min before measurements. Sampling occurred on sunny days between 10:00 and 18:00 to capture peak photosynthetic activity. Photosynthetically active radiation (PAR) was measured using a Li-Cor LI-190R sensor (LICORbio Inc., Lincoln, NE, USA). After each light-phase measurement, the chamber was covered to create dark conditions (PAR < 1 μmol m^−2^ s^−1^), enabling separation of soil respiration from photosynthetic uptake. Incubations of 60–90 s were sufficient to capture flux changes while minimizing chamber heating and CO_2_ depletion. Soil moisture and temperature were recorded using a Stevens Hydra-Probe II (Stevens Water Monitoring Systems, Inc., Portland, OR, USA), and air temperature inside chambers with an Onset HOBO logger (Onset Computer Corporation, Bourne, MA, USA).

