#### 2.9.6. Environmental Data Analysis

Meteorological data from the Tempest and Campbell Scientific stations will be quality-controlled to identify and correct erroneous or missing values. Data will be averaged over 15 min intervals for analysis. Two primary analyses are planned: (1) Intra-park analysis—hourly park-wide temperature averages on synoptically stable days (clear skies and calm conditions) will be compared across stations to identify spatial variability due to shading, ventilation, and ground cover. Anomalies relative to park-wide averages will be correlated with solar radiation, wind speed, and ground cover type; and (2) Post-intervention analysis—post-planting data will be compared with baseline measurements to quantify immediate and long-term microclimate effects of the intervention. Long-term trends will be assessed using the central Campbell Scientific station, with monthly statistics computed for all variables. Data will be compared with other stations in the University of Louisville network and with National Weather Service stations to evaluate the microforest’s contribution to reducing the urban heat island effect. Statistical comparisons will use nonparametric tests (e.g., Wilcoxon rank-sum), with significance defined as *p* < 0.05.

Biological and Ecological Data Analysis Avian data will be analyzed in RStudio (v4.3.1) to compare species abundance and diversity across sites ([name] Microforest, University Quad, Nettleroth Sanctuary). Microsoft Excel will support visualization. Surveys will continue after planting to assess temporal changes in avian presence.

Soil flux data (CO_2_ and CH_4_) will be analyzed using multiple linear regression models, with explanatory variables, including vegetation presence, soil moisture, soil temperature, and photosynthetically active radiation (PAR). Variables showing multicollinearity (r ≥ 0.60) will not be included in the same model. Candidate models will be evaluated using Akaike’s Information Criterion corrected for small sample size (AICc), with models within ΔAICc < 2 considered equivalent.

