**Figure 6 ijerph-23-00365-f006:**
[figure not shown]

[figure not shown]
Schematic of the microforest planting design. Panels depict a high-density, multilayered planting arrangement of (**A**) trees and (**B**) shrubs modeled after natural forest succession.

**Table 1 ijerph-23-00365-t001:** Summary table outlining research aims, hypotheses, and outcome measures.

Aim	Hypothesis	Exposure	Outcome Measures
Primary Aim 1	Exposure to microforest improves HRV and lowers BP vs. parking lot	Microforest vs. impervious site	heart rate variability (HRV) and blood pressure (BP)
Secondary Aim 2	Exposure to microforest improves stress responses and decreases VOC exposure	Microforest vs. impervious surface	Salivary cortisol, urinary catecholamines and their metaboiltes, urinary VOC metabolites, self-reported stress and rumination.
Exploratory Aim 3	Microforest reduces heat and pollution	Pre/post intervention; spatial monitoring, comparison with adjacent impervious surface.	Temperature, humidity, PM, NO_2_, BC
Exploratory Aim 4	Microforest enhances ecological function	Pre/post intervention	Avian diversity, microbiome composition, GHG flux, ecosystem services
Integrated Aim 5	Environmental modification mediates physiological benefits	Integrated environmental metrics	HRV, BP with environmental covariates

**Table 2 ijerph-23-00365-t002:** Meteorological variables recorded by Tempest and Campbell Scientific stations (temperature is measured with passively aspirated sensors in the Tempest stations and with fan-aspirated sensors in the Campbell Scientific station).

Variable	Tempest Stations	Research Station
Temperature (°C)	Passively Aspirated	Fan-Aspirated
Relative Humidity (%)	Passively Aspirated	Fan-Aspirated
Barometric Pressure (hPa)	√	√
Wind speed (m s^−1^)	√	√
Wind Direction (°)	√	√
Dewpoint Temperature (°C)	Calculated	Calculated
Solar Radiation (W m^−2^)	√	√

**Table 3 ijerph-23-00365-t003:** Demographic characteristics of study participants in Wave 1 (2023) and Wave 2 (2024).

	Wave 1 (2023)	Wave 2 (2024)
Age	39 [28 to 42]	42 [29 to 52]
Sex		
Male	16 (40%)	20 (40%)
Female	24 (60%)	30 (60%)
Race		
NHW	30 (75%)	28 (56%)
NHB	3 (8%)	10 (20%)
HW	0 (0%)	3 (6%)
HB	0 (0%)	0 (0%)
Other	7 (17%)	9 (18%)
Education		
≤4-year degree	21 (53%)	27 (56%)
>4-year degree	19 (47%)	22 (44%)
Income		
<$90 K	19 (47%)	27 (54%)
>$90 K	18 (45%)	21 (42%)
Declined/Don’t know	3 (8%)	2 (4%)

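### The dark-phase chamber CO2 flux is labelled soil respiration, but on vegetated collars it is soil plus enclosed-plant respiration

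*Protocol article*

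**What the plan says.** Section 2.4.2 opens by presenting the gas measurements as an assessment of soil microbial activity and gas fluxes. The chambers "allowed solar penetration and captured plant–soil gas exchange". The sign rule is: "Net emissions were inferred from increasing chamber concentrations, while decreasing levels indicated uptake". After every light-phase reading the same chamber is covered until PAR is below 1 μmol m⁻² s⁻¹, and this step is described as "enabling separation of soil respiration from photosynthetic uptake".

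Table 1 places the measurement in Exploratory Aim 4, a pre/post comparison under the hypothesis that the microforest enhances ecological function. Its outcomes are listed as "Avian diversity, microbiome composition, GHG flux, ecosystem services". Section 3 (Expected Results) again names soil microbial activity among the baseline surveys against which later change will be judged.

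Section 2.9.6 refers to soil flux data and regresses CO2 and CH4 flux on predictors that include vegetation presence, soil moisture, soil temperature and PAR. Section 2.4.4 estimates annual carbon sequestration separately, from the tree inventory in i-Tree Eco.

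**The concern.** The label given to the dark phase does not match what the chamber encloses. If living shoots are inside when light is removed, they go on respiring, and their CO2 is added to that from the soil. Calling the total soil respiration credits plant activity to the soil.

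This matters for a pre/post aim because planting changes the ground layer. The article describes a central space mainly of grass and brick pavers before the intervention. During site preparation that zone was regraded and sown with grass, and it was later planted with trees, shrubs and hundreds of groundcover plants. If the amount of enclosed plant material differs between surveys, the dark flux changes even when the soil does not. A report that took the label at face value could present this as a change in soil respiration or microbial activity.

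**Working it through.** **1. What the two phases measure.** Write S for soil respiration (microbes and roots), P for respiration of the shoots inside the chamber, and G for their photosynthesis, with emission positive.

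- Light flux = S + P − G
- Dark flux = S + P
- Dark minus light = G

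The light/dark pair separates photosynthesis (G) from total respiration (S + P). It does not separate S from anything unless P = 0, which means no living shoots in the collar. Section 2.4.2 states that plants are enclosed and that the dark reading follows the light reading under the same chamber, so P > 0 on vegetated collars.

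**2. Size of the mislabelling.** The share of the dark flux that is not soil is P / (S + P). The documents give neither S nor P. To show how the formula behaves, take S = 4 arbitrary units and P = 0.5, 1, 2 or 4 (all assumed):

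- 0.5 / 4.5 = 11%
- 1 / 5 = 20%
- 2 / 6 = 33%
- 4 / 8 = 50%

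These are not estimates for this site. Only the sign is established.

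**3. Effect on the pre/post comparison.** Hold S fixed and let enclosed-plant respiration go from P₁ to P₂. The change in dark flux is (S + P₂) − (S + P₁) = P₂ − P₁. Under the present label this whole change would be read as a change in soil respiration. It may be positive or negative, depending on how ground cover in the collars changes.

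**4. What fits in the chamber.** Inputs from 2.4.2 are volumes of about 5.7 L and 4.6 L and collar diameters of 27 cm and 22 cm. Assume straight sides, the collar footprint, and pairing in the listed order. Height = volume / (π × (diameter/2)²).

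- 5,700 cm³ / 572.6 cm² = 9.96 cm (9.9 to 10.0 cm, allowing for rounding of the volume)
- 4,600 cm³ / 380.1 cm² = 12.10 cm (12.0 to 12.2 cm)
- Opposite pairing: 5,700 / 380.1 = 15.0 cm and 4,600 / 572.6 = 8.0 cm

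In either pairing the chambers take in low ground cover and cannot take in trees or, in general, shrubs. Chamber CO2 is therefore a ground-layer flux.

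**The case against.** The strongest reply is that this is loose terminology in one exploratory outcome. The regression in 2.9.6 models CO2 and CH4 flux, not a variable named soil respiration. Its vegetation-presence term is meant to carry vegetation-related differences, PAR is a candidate predictor, and the term suggests that collars with and without plants are compared. Clipping and collar placement may be set out in a fuller protocol. Most of this stands, and it limits the point to interpretation. It does not rescue the label, because the article itself says that plants were enclosed and that the same chamber was then covered.

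A reader might infer more than the documents support:

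- *That the endpoint could show the opposite of the site's true CO2 change.* The article never calls chamber flux the site's CO2 balance, states no expected direction for it and sets no scoring rule. A reversal needs flux values that the documents do not give. The baseline was also not treeless, since 24 mature trees stood there. The new groundcover can fit in the chambers and could raise ground-layer uptake.
- *That the study misses tree uptake.* The chamber does not see it, but i-Tree Eco estimates tree sequestration separately, and ecosystem services are a separate outcome of the same aim. The described inventory covers trees, so shrub uptake is the part without a described estimate.
- *That root respiration is mislabelled.* It is ordinarily part of soil respiration. Only enclosed-shoot respiration is wrongly named.
- *That plant respiration inflates net emission in the light.* In that phase it is offset by the photosynthesis of the same plants.
- *That a percentage overstatement can be quoted.* Any such figure rests on an assumed plant share.

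**Conclusion.** The point holds as a labelling and interpretation error. On vegetated collars the dark CO2 flux is soil plus enclosed-plant respiration. Soil respiration is overstated there by an unknown positive amount, and a change in ground cover can pass for a change in the soil. The same applies to soil microbial activity where it is read from these data.

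The conclusion rests on the article's own statement that plants and soil are enclosed together, and on shoots continuing to respire in the dark. The ground-layer reading also rests on the 10 to 12 cm chamber height, with the assumptions on shape and pairing given above. The argument concerns CO2 and does not reach CH4. It affects one outcome of Exploratory Aim 4 and leaves the primary analyses untouched. The importance is minor.

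**What to change.** In 2.4.2 and 2.9.6:

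1. Call the dark CO2 flux *soil plus enclosed-plant respiration*, and say that the light/dark difference estimates photosynthesis of the enclosed plants.
2. Confine statements about soil respiration or soil microbial activity to collars without vegetation.
3. Describe chamber CO2 as a ground-layer flux. State that it is not to be read as the site's net CO2 change without the i-Tree tree estimate already planned, and note that no estimate of shrub uptake is described.

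No new measurements are needed. The cost is a narrower claim for one exploratory outcome. If few collars are free of vegetation, there will be little to say about soil respiration alone.

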#### 2.4.3. Soil Sampling and Microbiome Characterization

We are also assessing microbial (bacterial and fungal) community composition and diversity in the microforest over time. This is being done to characterize microbial community health and composition pre- and post-intervention as an exploratory outcome related to ecosystem resilience. Samples were and will be repeatedly taken from the site over time from the same locations; these sample sites cover each corner of the site, as well as the center. From each collected soil sample, we take a 0.25 g subsample of soil and extract genomic DNA using the Qiagen DNeasy^®^ PowerSoil^®^ Kit (Qiagen N.V., Hilden, Germany) following the manufacturer’s guidelines. DNA will be shipped to the W. M. Keck Center for Comparative and Functional Genomics at the University of Illinois, Urbana-Champaign, for Fluidigm amplification, followed by Illumina NovaSeq 6000 sequencing. For bacteria, we will amplify the 16S rRNA region using primer pair V4_515F_806R_New (V4_515F_New 5′-GTGYCAGCMGCCGCGGTAA, V4_806R_New 5′-GGACTACNVGGGTWTCTAAT). For fungi, we will amplify the internal transcribed spacer (ITS) region using primer pairs for ITS1 (ITS1F_ITS2, ITS1F 5′-CTTGGTCATTTAGAGGAAGTAA, ITS2 5′-GCTGCGTTCTTCATCGATGC), and ITS2 (ITS3_ITS4, 5′-GCATCGATGAAGAACGCAGC, ITS4 5′-TCCTCCGCTTATTGATATGC).

#### 2.4.4. Tree Inventory and Ecosystem Services

To quantify ecosystem services, all trees at the site were inventoried. Species were identified, and diameter-at-breast-height (DBH) and crown health (dieback %) were recorded. The U.S. Forest Service i-Tree Eco software (v6.1.47) was used to estimate annual carbon storage and sequestration, pollution removal, oxygen production, and prevented runoff. Carbon storage represents the stock released upon tree death and decomposition, while sequestration reflects annual CO_2_ uptake. Pollution removal estimates were based on species, size, and canopy characteristics. Oxygen production was derived from sequestration data, and prevented runoff was estimated from canopy cover, species type, and crown conditions.

### 2.5. Human Study Design and Participants

#### 2.5.1. Study Design and Timeline

The GRO Project is a randomized crossover study of healthy adults aged 18–75 years. Baseline data were collected in two clinical waves prior to installation of the microforest: Wave 1 (Summer 2023) and Wave 2 (Summer 2024). To evaluate the intervention, a follow-up study is underway in Summer 2025 (Wave 3), with additional longitudinal assessments planned for Summers 2026 and 2027 (Waves 4 and 5).

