### 2.3. Environmental Data Collection

#### 2.3.1. Meteorological Monitoring

To capture meteorological conditions, we deployed two types of weather stations: a WiFi-based “prosumer” system (Tempest Weather Station, WeatherFlow Inc., Santa Cruz, CA, USA) and a research-grade system (Campbell Scientific Inc., Logan, UT, USA). The Tempest stations record a wide range of variables (Table 2) at 1 min intervals and automatically transmit data to a hub and redundantly log in cloud storage. In summer 2023, six Tempest stations were installed, four at the corners of the site and two near the center, allowing measurements across varied shade and ground-cover conditions.

To ensure accuracy and provide long-term monitoring, a Campbell Scientific research-grade station was installed at the site’s center. This station records many of the same meteorological variables as the Tempest, but its temperature sensor is housed in a fan-aspirated shield to prevent stagnation bias. Data are recorded at 1 min intervals and manually downloaded from the datalogger. A fine temporal resolution is used, corresponding to participant exposure periods as part of the human crossover component. Site-wide microclimatic analysis will use hourly and daily data, which can be aggregated into monthly datasets for long-term analysis. Both the Tempest and Campbell systems collected baseline data until site construction began. The central research station and two Tempest units were removed for construction; the research station was reinstalled in December 2024, while the central Tempest stations were permanently eliminated from the final design (Supplemental Figure S1).

During the second round of clinical trials, before the Campbell station was reestablished, a mobile cart system was developed to replicate the fixed-station measurements. This was done to ensure continuity of meteorological measurements when the central fixed station had to be removed during construction. The mobile unit collected equivalent variables at 1 min intervals and was activated at least 30 min before participant arrival to ensure stabilization. In parallel, one researcher wore an AirBeam3 device during participant walks, providing second-by-second measurements of particulate matter (PM_1_, PM_2.5_, and PM_10_).

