### 2.8. Greening Intervention: The [name] Microforest

#### 2.8.1. Site Preparation and Infrastructure

The intervention began after completion of the first round of baseline testing in Summer 2023. Initial site modifications included the removal of the existing central walkway and the installation of a semi-circular retaining wall, along with a new perimeter walking path (Figure 5). The retaining wall is three feet tall and spans 188 feet, and the wall’s thickness varies from one to two feet to support the weight of the new soil. Benches and lighting were added, and the retaining wall was backfilled with approximately 700 tons of Nugent soil to create a three-foot raised area sloping southward. In addition, metal signage and fins were installed on the south side of the retaining wall to complete the circle, with the signage being 66 inches in height and four inches thick, and the metal fins being 60 inches in height and one inch thick (Supplemental Figure S2). This middle well zone was planted with grass, and mulch was applied along the park’s edges prior to the wave 2 physiological assessment in Summer 2024.

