#### 2.8.2. Planting Design and Species Composition:

The primary phase of greening occurred in Winter 2024 and extended into the following months. A total of 119 trees representing 31 species were planted (Supplementary Table S2), comprising a mix of deciduous (primarily Anacardiaceae, Fabaceae, and Fagaceae families) and evergreen species (mainly Pinaceae). This combination was selected to maximize cooling benefits in a temperate climate and enhance year-round canopy cover. In addition, 242 shrubs and hundreds of herbaceous groundcover plants were installed across the site (Supplementary Table S3). Plant material was sourced from nurseries in multiple states and transported directly to Louisville to minimize storage stress prior to planting.

Trees were planted in close spacing (1–1.5 m apart) to accelerate canopy closure. Shrubs were positioned between rows to form a layered understory, while herbaceous species and groundcovers filled interstitial spaces. This stratified planting scheme was designed to mimic natural forest succession, increase soil infiltration, suppress weeds, and promote early biodiversity. Collectively, these dense plantings are expected to enhance evapotranspirative cooling, mitigate urban heat, and improve ecosystem resilience (Figure 6A,B). Progress of installation is shown in Figure S3.

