#### 2.9.5. Exploratory Neighborhood-Level Analyses

Time series data from site monitors and regional models will be used to assess the broader impact of the microforest on local climatic conditions. Two reference groups will be used: (1) Founders Square pre-intervention and (2) the adjacent parking lot. Interrupted time series regression will estimate intervention effects, with the planting date as the interruption point. Weekly aggregated data will be analyzed, and Fourier terms will capture seasonal variation. Future analyses may also explore changes in human mobility patterns, using cluster analysis of objective measures (e.g., GPS or cellular trace data) to identify microforest features most associated with increased visitation. We will use an interrupted time series analysis to evaluate the effectiveness of the microforest intervention on lowering regional temperatures and pollution levels [60]. The interrupted time point will be defined as the date of the microforest planting. Time series data will be aggregated to weekly values pre- and post-intervention for analysis. We will fit Fourier terms in our model to capture seasonal patterns in our data [61]. In future exploratory analyses, we could also consider examining the effect of specific aspects of the greening intervention on human mobility patterns. We will use cluster analysis to identify the specific characteristics of the microforest and its environment that are most strongly associated with changes in human mobility patterns. We can use objective measures of mobility, such as GPS tracking or cellular phone traces, to determine the frequency and duration of visits to different types of green spaces. This analysis will help us to better understand the mechanisms underlying the relationship between green space and health [62,63].

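### Wave 2 and the construction period count as pre-intervention, although the article dates the start of the intervention to after Wave 1

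*Protocol article*

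**What the plan says.** The protocol article marks the start of the intervention in two ways.

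**By planting.** Section 2.5.1: "Baseline data were collected in two clinical waves prior to installation of the microforest: Wave 1 (Summer 2023) and Wave 2 (Summer 2024". The abstract likewise places the baseline in 2023 and 2024. Section 2.9.5 specifies the interrupted time series "with the planting date as the interruption point", using weekly values split into pre and post and naming no transition period. Section 2.8.2 dates the planting: "The primary phase of greening occurred in Winter 2024 and extended into the following months".

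**By site works.** Section 2.8.1, under the heading for the greening intervention: "The intervention began after completion of the first round of baseline testing in Summer 2023". The first works were the "removal of the existing central walkway and the installation of a semi-circular retaining wall", followed by a perimeter path, benches, lighting and about 700 tons of soil forming a raised area. Grass in the middle zone and mulch at the edges were in place "prior to the wave 2 physiological assessment in Summer 2024". Section 2.3.2 describes one LiDAR scan as "another in May 2024 during construction". Section 2.3.1 ends the meteorological baseline when construction began and adds: "The central research station and two Tempest units were removed for construction". The central station returned in December 2024.

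Section 2.9.2 puts study wave into the primary model as a covariate, and the only reason given is the change of blood pressure device between Waves 1 and 2.

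**The concern.** A before/after comparison is a stated part of the design: the Introduction describes walking before and after installation, and Table 1 gives pre/post intervention as the exposure for Exploratory Aims 3 and 4. What counts as before decides which effect is reported.

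The site at Wave 2 was neither the original park nor the planted microforest. Relief, ground cover and walking path had all been changed by works that the article itself calls the intervention. If those works made the site hotter or less pleasant, a baseline that includes Wave 2 makes the later gain look too large. If the new path and grass helped, it makes the gain look too small. The same applies to the time series if construction weeks sit before the break.

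**Working it through.** The article gives no figure on this point to reproduce. The check sets the dated statements against each other, counts the data affected, and illustrates the effect on the time series.

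**1. Order of events.** Wave 1 (Summer 2023, section 2.5.1); intervention begins (section 2.8.1, no date); construction under way by May 2024 (section 2.3.2); grass and mulch, then Wave 2 (Summer 2024, section 2.8.1); wall complete and backfilled in an August 2024 photograph (Figure 5 caption); main planting in Winter 2024 and the months after (section 2.8.2). Wave 2 thus falls after the stated start of the intervention and before the main planting.

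**2. Share of the clinical baseline.** Inputs from section 2.6.1: 40 in Wave 1, of whom 25 returned, and 25 new in Wave 2.
- Wave 2 size: 25 + 25 = 50.
- Share of pre-planting participant-waves: 50 / (40 + 50) = 56%.
- Distinct people: 40 + 25 = 65. Those with no measurement on the original site: 25 / 65 = 38%.

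**3. Does the wave covariate repair this?** No. A wave main effect shifts both sites equally within a wave, so it cannot show how the site-versus-lot difference changes with the state of the site. The device change and the site change also fall between the same two waves, so that term cannot separate them.

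**4. Construction weeks before planting.** Assumed dates, since the article gives none exactly: monitoring from 1 June to 1 August 2023, construction start from 1 September 2023 to 1 May 2024, planting from 1 December 2024 to 1 March 2025. Share = (planting − construction start) / (planting − monitoring start).
- Lowest: 1 May to 1 December 2024 is 214 days (31 weeks); 1 June 2023 to 1 December 2024 is 549 days (78 weeks); 214 / 549 = 39%.
- Highest: 1 September 2023 to 1 March 2025 is 547 days (78 weeks); 1 August 2023 to 1 March 2025 is 578 days (83 weeks); 547 / 578 = 95%.
- Weeks before construction: 4 to 48 across the scenarios.

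**5. Illustration of the planting-date break.** Noise-free weekly series from 15 June 2023 to 1 September 2027, planting on 15 December 2024, two annual Fourier harmonics, and a step at planting. The true total change from original to planted site is 1.0. Ranges cover construction starts of 1 September 2023, 1 January 2024 and 1 May 2024.

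| True change at construction / at planting | Step only | Step with segment trends |
|---|---|---|
| 0 / 1.0 | 1.00 | 1.00 |
| 0.5 / 0.5 | 0.58 to 0.80 | 0.30 to 0.44 |
| −0.5 / 1.5 | 1.20 to 1.42 | 1.56 to 1.70 |

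In the last two rows the estimate matches neither the total change (1.0) nor the planting-only change (0.5 or 1.5). With the construction weeks left out, every case returns 1.00. The split between construction and planting is assumed; the article gives no information on it.

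**The case against.** The strongest defence is that section 2.5.1 speaks of installing the microforest, and if that means planting trees, Wave 2 did come first. This is literally true, but it leaves the conflict in place, because section 2.8.1 counts the earlier works as the intervention and those works changed the site.

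For the time series, section 2.3.1 can be read as all site baseline data ending when construction began. There would then be a gap and no contamination. That reading is possible, but the article states removal only of the central station and two of six Tempest units, and section 2.9.5 also draws on regional models. On the text as written, any weeks that were recorded fall before the break.

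Several stronger readings are tempting and not supported:
- That Wave 2 was walked on bare soil. Section 2.8.1 says grass had been planted.
- That the intervention began about a year before Wave 2. The text fixes only a start after Wave 1 and construction under way by May 2024.
- That the baseline is shifted by 56% of any construction effect. No section specifies a pooled mean of Waves 1 and 2.
- That the Fourier terms rest on construction weeks. Common seasonal terms also draw on the post-planting weeks.
- That the primary comparison fails. Primary Aim 1 contrasts microforest with parking lot within person, and the order of sites is randomized.

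It is also fair to say that the time series is labelled exploratory, and that section 2.9.5 already names the adjacent parking lot as a second reference.

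**Conclusion.** The concern holds for the before/after contrast and the exploratory time series. The article gives two starting points for the intervention, and the one used for analysis puts construction-phase data on the pre side: 50 of 90 pre-planting participant-waves and, for monitors that stayed in place, roughly 39% to 95% of pre-planting weeks. The first figure comes directly from section 2.6.1; the second depends on the assumed dates. The direction of any bias is unknown, and there is none if construction left conditions unchanged. The randomized within-wave comparison stands.

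**What to change.** 1. Define the start of the intervention once, give the calendar dates of construction start and completion of planting, and use the same definition in the abstract and sections 2.3.1, 2.5.1, 2.8.1 and 2.9.5. Check the label on the February to April 2024 avian surveys (section 2.4.1) against those dates.
2. Code site state at three levels: original (Wave 1), constructed but without the tree planting (Wave 2), and planted (Wave 3 onward).
3. Estimate pre/post change through a treatment-by-site-state term. Take planted versus original as the intervention contrast and planted versus constructed as the planting-only contrast.
4. In the time series, exclude the interval from construction start to completion of planting, or give it its own segment.

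This changes analysis wording and needs no new data. The cost is precision: the clean baseline falls from 90 participant-waves to the 40 of Wave 1. How much precision is lost depends on within-person correlation and on how many people return, neither of which the article gives. Blood pressure contrasts against Wave 1 also remain confounded with the device change, so they need the device sensitivity analysis of section 2.9.2 and cautious reading.
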